### Eligibility Criteria

The inclusion criteria for the target trial are the same as those for NuAge [25]. In the emulation, participants will be required to have at least one 24-hour dietary recall completed at baseline with ≥500 calories, as well as complete covariate data at baseline, as identified in the *Assignment* section.

### Hypothetical Interventions

#### Overview

The hypothetical intervention strategies evaluated will be as follows:

No change in dietary habits or physical activity (similar to a control intervention)Adherence to CFG recommendationsAdherence to CFG recommendations, including reformulation (ie, higher intake of protein foods)Adherence to CFG recommendations, including reformulation (ie, higher intake of protein foods) and performing at least 30 minutes of aerobic physical activity

Physical activity recommendations are not traditionally at the forefront of CFG recommendations. However, CFG does mention that “at least 150 minutes of moderate-to vigorous-intensity aerobic physical activity per week ... is recommended to achieve health benefits” [1]. Thus, recognizing the key role of exercise in maintaining health and muscle for older adults, the fourth hypothetical intervention includes a formal physical activity recommendation. In the target trial, the physical activity corresponds to performing aerobic exercise of light to vigorous intensity for at least 30 minutes per day [6].

#### The Challenge of a Well-Defined Nutritional Intervention

Emulating a well-defined dietary intervention for CFG recommendations is challenging. First, recommendations in the latest edition of CFG are qualitative and flexible (eg, “eat plenty of vegetables and fruits” [1,29]). Thus, various suitable yet distinct dietary patterns can align with the recommendations. Second, CFG recommendations target both food intakes (eg, vegetables and fruits) and nutrients (eg, saturated fats). The nutrient-based recommendations can be met by modifying the consumption of various foods. For example, to achieve the hypothetical intervention of “decreasing consumption of calories from saturated fats,” one could decrease saturated fats from dairy, nuts, and low nutritive value foods altogether. Arguably, the relationship between these food categories and a given health outcome may vary greatly.

To estimate a causal effect using observational data, the hypothetical interventions must be clearly defined to the point where “no meaningful variation” in the intervention remains [30,31]. In other words, the hypothetical diet interventions should be elaborated until no additional dietary characteristics are deemed impactful regarding the outcome of interest. Another consideration is that the modeling of hypothetical interventions should ideally be conducted with dietary intakes expressed using the same units. For example, mixing food intakes expressed in servings and grams in a statistical model may cause poor estimation of causal effects [17]. Finally, the statistical approach used to account for total energy or total food intake also affects the causal effect of interest and should be consistent with the research question [17,31-33].

#### Diet Simulations

For this study, adherence to CFG recommendations was defined based on simulated diets generated by Health Canada [34] and summarized in Multimedia Appendix 1 [34]. The simulated diets were designed to meet CFG recommendations on healthy food choices and nutrient requirements (Dietary Reference Intake).

These diets achieve near-perfect Healthy Eating Food Index (HEFI)-2019 scores (>78/80) through relatively high intake of recommended foods (ie, vegetables and fruits, whole grain foods, protein foods, and unsweetened milk and plant-based beverages with protein) and null intakes of foods not recommended (ie, non–whole grain foods; other low nutritive value foods; juice, sugary drinks and alcohol; and fatty foods rich in saturated fats). The HEFI-2019 score indicates the extent to which dietary intakes are consistent with CFG recommendations on healthy food choices [29,35].

Notably, the HEFI-2019 could have been used as a main exposure to measure adherence to CFG. However, the use of a composite score metric would not completely satisfy the criterion of a well-defined intervention to estimate a causal effect. First, high HEFI-2019 scores and high adherence to CFG recommendations can be achieved through many different strategies or dietary patterns. In the context of observational data, the specific strategies through which individuals achieve a high HEFI-2019 score would be based on dietary habits and patterns self-selected by the participants. This approach is similar to asking hypothetical trial participants to modify their intakes without clearly specifying how, which would obscure the estimated causal effect. Second, the HEFI-2019 score includes recommendations on foods and nutrients. As described earlier, mixing servings and grams in statistical models may cause poor estimation of causal effects [17].

We stress that the diets simulated by Health Canada were not actually consumed by older adults. Therefore, the simulated values for vegetables and fruits, whole grain foods, and plant-based protein foods *exceed* the 99th percentile of the distribution of usual intakes of these food categories, as estimated in adults aged ≥65 years from the Canadian Community Health Survey 2015–Nutrition [3]. In Table 2, the target intakes for vegetables and fruits, whole grains, and plant-based protein foods in the adherence to the 2019 CFG recommendations intervention were revised to correspond, at most, to the 90th percentile of the distribution of usual intakes among Canadians aged ≥65 years in 2015 [3].

**Table 2 table2:** Emulation^a^ of hypothetical diet and exercise interventions by sex in the Quebec Longitudinal Study on Nutrition and Successful Aging (NuAge) cohort [25].

Sex		Recommended foods (RA^b^/d)							Dietary supplement^c^		Foods and beverages not recommended (RA/d)^d^					Physical activity (min/d)^e^
		Vegetables and fruits	Whole grains	Plant-based protein foods	Animal-based protein foods	Milk and plant-based beverages with protein	Unsaturated oils and fats			Other foods		Sugary drinks and alcohol	Non–whole grains			
**Control (no change)^f^**																
	Male individuals	—^g^	—	—	—	—	—	—		—		—	—		—	
	Female individuals	—	—	—	—	—	—	—		—		—	—		—	
**Adhering to the 2019 Canada's Food Guide recommendations on healthy food choices^h^**																
	Male individuals	6	1.5	1.0	2.0	1.0	1	No change		Minimum		Minimum	Minimum		No change	
	Female individuals	5	1.5	0.8	1.5	1.0	1	No change		Minimum		Minimum	Minimum		No change	
**Adhering to the 2019 Canada's Food Guide recommendations on healthy food choices, including extra protein^i^**																
	Male individuals	6	1.5	1.5	3.5	1.5	1	No change		Minimum		Minimum	Minimum		No change	
	Female individuals	5	1.5	1.3	3.0	1.5	1	No change		Minimum		Minimum	Minimum		No change	
**Adhering to the 2019 Canada's Food Guide recommendations on healthy food choices, including extra protein and physical activity**																
	Male individuals	6	1.5	1.5	3.5	1.5	1	No change		Minimum		Minimum	Minimum		30 or more	
	Female individuals	5	1.5	1.3	3.0	1.5	1	No change		Minimum		Minimum	Minimum		30 or more	

^a^The emulation of all hypothetical interventions will be implemented using a substitution approach in statistical models. In all models, 1 variable for total food intake and 1 variable for total beverage intake will be included, and foods not recommended will be left out from the models (ie, non–whole grain foods; other low nutritive value foods; juice, sugary drinks and alcohol; and fatty foods rich in saturated fats).

^b^RA: reference amount.

^c^Dietary supplements were not intervened on but were, nonetheless, excluded from foods and beverages not recommended to avoid being considered in the substitution. In other words, participants would not be instructed to modify their dietary supplements in the hypothetical trial.

^d^Minimum indicates that consumption would be set at the smallest amount, permitting a concomitant increase in recommended foods to meet Canada’s Food Guide targets. Portions for foods not recommended may vary on an individual basis.

^e^Physical activity corresponds to aerobic exercise of moderate or higher intensity [6].

^f^Values will be the averages observed at baseline in the NuAge cohort. In other words, values will be the observed intakes for the food categories or amount of physical activity when no change is applied.

^g^Not applicable.

^h^Values are derived from Health Canada’s simulated composite diets of adults aged ≥71 years. Participants would be expected to meet these targets for each food category. The specific food choices within these categories would be at the participants’ discretion. Values for vegetables and fruits, whole grain foods, and plant-based protein foods were truncated to correspond, at most, to the 90th percentile of the distribution of usual intakes among Canadians aged 65 years in 2015.

^i^Extra protein foods were added as follows: +0.5 RA of plant-based protein foods (eg, 25 g of nuts), +1.5 RA of animal-based protein foods (eg, 150 g of cooked unprocessed red meat, fish, or poultry or 3 small eggs), +0.5 RA of milk or plant-based beverage with protein (eg, 125 mL of milk or plant-based beverages with sufficient protein).

Because the 2019 CFG does not have a portion size system, reference amounts (RAs) were used as a proxy for servings. RAs are regulated quantities of foods that reflect the portion size typically consumed at 1 sitting in Canada. RAs were used by Health Canada to simulate a diet consistent with the 2019 CFG recommendations and dietary reference intake (Multimedia Appendix 1 [34]); therefore, RAs are adequate for this study.

#### Implementation

In the target trial, the sustained intervention strategy could be implemented as follows:

Step 1: the participants’ usual dietary intake and physical activity would be assessed by research dietitians at each study visit.Step 2: if reported food intakes and duration of physical activity were equal to or above the prespecified thresholds (Table 2), no change would be suggested to the participants’ diet or physical activity. If food intakes or duration of physical activity were below the prespecified thresholds, participants would be instructed to increase food consumption to exactly the prespecified portions or increase physical activity duration to 30 minutes per day (when applicable).Step 3: if changes are required, participants would be instructed to decrease consumption of foods not recommended by the same amount as the increase in step 2. For example, if a 2-serving increase in vegetables and fruits is required to meet the prespecified intervention thresholds, participants would be instructed to substitute 2 servings of vegetables and fruits for non–whole grain foods; other low nutritive value foods; juice, sugary drinks and alcohol; and fatty foods rich in saturated fats.

In the emulation, for all hypothetical interventions, substitution will be implemented by including total intakes as a covariate and excluding foods not recommended from the models. More precisely, a variable reflecting total food intake (in RA/d) and a variable reflecting total beverage intake (in RA/d) will be included in all models. Hence, total food and beverage intakes will be constant across hypothetical diet interventions. In this approach to account for total energy, all model coefficients reflect the action of increasing intakes of recommended foods and a concomitant decrease in *any* of the foods not recommended [32]. On one hand, this approach can be potentially confusing [17,33], as the default interpretation of model coefficients assumes increasing the intake of each *food included in the model* while simultaneously decreasing the intake of foods *excluded from the model* [32]. On the other hand, the standard model is generally consistent with the implementation of dietary intervention in feeding trials [16,36,37]. The standard model also reduces the number of variables to be considered as intervention variables. Otherwise, 4 additional dietary components would have to be modeled for foods not recommended (ie, non–whole grain foods; other low nutritive value foods; juice, sugary drinks and alcohol; and fatty foods rich in saturated fats). Finally, the explicit description of the intervention strategies in the target trial protocol clarifies the estimand of interest, as done in an earlier study [19,31].

Notably, nutrient-based recommendations in CFG (ie, saturated fats, free sugars, and sodium intake) are not explicitly modeled to avoid the problems associated with mixed-unit models [17]. In the target trial, we assume that nutrient-based targets would be met by reducing consumption of foods not recommended (ie, non–whole grain foods; other low nutritive value foods; juice, sugary drinks, and alcohol; and fatty foods rich in saturated fats). In that regard, food-level substitution analyses in Canadians support this assumption for saturated fats [38,39].

The extra protein intervention consists of increasing the intake of both animal-based and plant-based protein foods by 1.5 and 0.5 RA per day, respectively, as well as milk and plant-based beverages with sufficient protein by 0.5 RA per day. Regarding the amount of food, this corresponds to adding 150 g of cooked unprocessed red meat, fish, or poultry or 3 small eggs; 25 g of nuts and seeds; and 125 mL of milk or plant-based beverages with sufficient protein while proportionally decreasing the intake of foods not recommended. In a previous RCT [40], older women aged 60 to 90 years were able to consume an additional 160 g of cooked lean red meat without substitution, thereby supporting the feasibility of the protein intervention in this hypothetical study.

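### Holding total food constant while raising every Table 2 floor gives a negative amount of foods not recommended for anyone with too little to displace, and nothing in the stated emulation bounds or shows this

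*Protocol article*

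**What the plan says.** Table 2 of the protocol article sets simultaneous minimum intakes for six recommended categories. For men the floors are "6 1.5 1.0 2.0 1.0 1" in strategy 2 and "6 1.5 1.5 3.5 1.5 1" in strategies 3 and 4. For women they are "5 1.5 0.8 1.5 1.0 1" and "5 1.5 1.3 3.0 1.5 1". The columns run: vegetables and fruits, whole grains, plant protein, animal protein, milk and plant-based beverages, unsaturated fats.

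The Implementation section gives the rules. In Step 2, a category at or above its floor is left alone; below it, "participants would be instructed to increase food consumption to exactly the prespecified portions". In Step 3, "participants would be instructed to decrease consumption of foods not recommended by the same amount as the increase in step 2".

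The same section then describes the emulation. One variable for total food and a separate one for total beverages enter every model, and foods not recommended are excluded. The article concludes: "Hence, total food and beverage intakes will be constant across hypothetical diet interventions".

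Footnote d of Table 2 says of foods not recommended that "consumption would be set at the smallest amount, permitting a concomitant increase in recommended foods", and that portions may differ between individuals. Diet Simulations caps three of the category targets at the 90th percentile of usual intake. Limitations allows targets to be revised if NuAge intakes turn out far from them.

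**The concern.** Three rules apply together in the emulation: every shortfall is raised to its floor, no category above its floor is lowered, and total food does not move. Foods not recommended must absorb the whole change, and they cannot go below zero. Where a person eats too little of them, the three rules describe a diet that cannot exist.

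The analysis would not reveal this. Foods not recommended are the omitted component, so the simulation never computes them. The model check described under Principal Findings compares observed with predicted time-varying covariates. It cannot flag an unmodelled quantity that turns negative only under intervention.

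The primary per-protocol contrast is at stake. For the affected person-visits it would be a prediction outside the set of feasible diets, although the article itself asks for well-defined interventions. The floors are highest in strategies 3 and 4, which carry Hypothesis 2.

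**Working it through.** **Inputs.** The floors are from Table 2. The rules are from the Implementation section. Milk and plant-based beverages are counted under the beverage total and oils under food. This is my reading of the two-total model; the article does not spell it out.

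**Identity.** With total food T fixed, foods not recommended after intervention are

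R = T − Σ max(intake, floor), which is at most T − Σ floor.

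So T below Σ floor is sufficient for R < 0. The exact condition is T below Σ max(intake, floor).

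**Solid-food floor sums (RA/d).**
- Strategy 2, men: 6 + 1.5 + 1.0 + 2.0 + 1 = 11.5
- Strategy 2, women: 5 + 1.5 + 0.8 + 1.5 + 1 = 9.8
- Strategies 3 and 4, men: 6 + 1.5 + 1.5 + 3.5 + 1 = 13.5
- Strategies 3 and 4, women: 5 + 1.5 + 1.3 + 3.0 + 1 = 11.8

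If milk counted as food, the sums would be 12.5, 10.8, 15.0 and 13.3 in the same order.

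**Two illustrations with assumed intakes (men, strategies 3 and 4).** Intakes are in the order vegetables and fruits, whole grains, plant protein, animal protein, oils.
- T = 12, intakes 4, 0.7, 0.4, 2, 0.5 (sum 7.6). Displaceable food: 12 − 7.6 = 4.4. Required increase: 2 + 0.8 + 1.1 + 1.5 + 0.5 = 5.9. R = 4.4 − 5.9 = −1.5.
- T = 14.5, the same except vegetables and fruits at 8 (sum 11.6). Displaceable food: 14.5 − 11.6 = 2.9. Required increase: 0.8 + 1.1 + 1.5 + 0.5 = 3.9. R = 2.9 − 3.9 = −1.0. This man is above 13.5 and still affected.

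**Possible size.** The article gives no distribution of total food in RA/d, so this is assumption only. For a normal total, the share below the sum is Φ((Σ floor − mean)/SD). For men in strategies 3 and 4 with mean 12 and SD 3: Φ((13.5 − 12)/3) = Φ(0.5) = 69%. With mean 18 and SD 3: Φ(−1.5) = 7%.

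| Percent below the sum (SD 3 / SD 4) | Mean 12 | Mean 14 | Mean 16 | Mean 18 |
|---|---|---|---|---|
| Men, strategies 3 and 4 | 69 / 65 | 43 / 45 | 20 / 27 | 7 / 13 |
| Women, strategies 3 and 4 | 47 / 48 | 23 / 29 | 8 / 15 | 2 / 6 |
| Men, strategy 2 | 43 / 45 | 20 / 27 | 7 / 13 | 2 / 5 |
| Women, strategy 2 | 23 / 29 | 8 / 15 | 2 / 6 | 0.3 / 2 |

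For any given mean and SD these shares are lower bounds, because they use the sufficient condition only.

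**The case against.** The strongest reply is that nobody knows whether this affects many people or few. That stands: the means and SDs have no anchor in the article, and a higher assumed mean shrinks the share quickly.

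A second reply is that the authors saw the feasibility problem. They truncated three targets, allowed portions to vary in footnote d, and kept a revision of targets open. This softens the point but does not resolve it. The truncation works one category at a time and does not check the sum. Footnote d presumes there is enough to displace and sets no rule for when it runs out. The revision clause gives no criterion and does not compare total food with the summed floors.

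A third reply is that a condensed article may leave bounds in the simulation code to fuller documents. That would answer a complaint about missing detail. Here, however, the rules as stated produce the infeasible prediction when they are followed.

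A reader might infer three stronger things that the article does not support:
- **That the model credits a benefit.** The sign of the relevant coefficients is unknown, and Hypothesis 1 expects no effect of strategy 2 on muscle health, which is the primary outcome domain.
- **That the error falls mainly on small eaters.** The second illustration shows that it can also reach someone above the sum.
- **That the target-trial instruction is itself impossible at these sums.** Step 3's example lets vegetables and fruits displace drinks, so the food-only bound applies strictly to the emulation, where the two totals are fixed separately.

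**Conclusion.** The point holds for the emulation. With constant total food, all floors met and no category lowered, any person-visit with total food below Σ max(intake, floor) is assigned a negative amount of foods not recommended. This includes everyone below 11.5 (men) or 9.8 RA/d (women) in strategy 2, and below 13.5 or 11.8 in strategies 3 and 4. The primary g-formula contrast then extrapolates to diets that cannot exist for those person-visits.

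The logic follows from Table 2 and the stated rules, given that milk belongs to the beverage total and oils to food. How often it happens cannot be found from the article: about 7% to 69% of men in strategies 3 and 4 under the assumed totals. The direction and size of any bias are unknown. Step 3 and the emulation also differ on whether drinks may be displaced by food, and this needs reconciling in its own right.

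**What to change.** 1. At each person-visit, compute foods not recommended as total food minus recommended foods, and do the same for beverages. State which total milk and oils belong to.
2. Report by strategy, sex and time point the share of person-visits in which the required increase exceeds that amount.
3. Add a sensitivity analysis of the primary contrasts in which the simulated remainder is kept at or above zero.
4. Reconcile Step 3, footnote d and the emulation paragraph, so that the target trial and the emulation treat the unmet remainder in the same way. The choice belongs to the investigators; no dietary target is proposed here, and the participant instruction need not be rewritten to run the check.

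The cost is a custom intervention function and one extra table, using data already collected. The downside is that some participants will be shown not to reach every target.

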The intention-to-treat analysis will be a secondary analysis of a hypothetical point intervention, for example, dietary counseling at baseline only. Notably, it will not be possible to conduct an intention-to-treat analysis identical to that of a controlled study where the interest is to estimate the effect of being *assigned* to an intervention [11]. However, it is possible to conduct an observational analog of the intention-to-treat analysis. In the observational analog, the intention-to-treat analysis aims to estimate the impact of a hypothetical intervention in which adherence is measured at baseline only.

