### Statistical Analysis

#### Modeling of Hypothetical interventions

Stratification and multivariable regression (ie, covariate adjustment) are conventional statistical approaches to address confounding in nutritional epidemiology. However, the conventional approaches are not adequate to estimate cumulative treatment effects (eg, diet over time) in the presence of time-varying confounding (eg, weight status over time) and treatment (eg, previous diet) [41,42]. In this study, nonadherence to the hypothetical interventions and incomplete follow-up will be considered using general g-methods for the per-protocol analysis [11,42]. Among g-methods, the parametric g-formula provides the most flexibility for analyses involving hypothetical dietary interventions, as used in previous studies [19,22,43]. Briefly, in the context of an observational study, the parametric g-formula and its implementation into an R package (R Foundation for Statistical Computing) [44] use parametric models to predict the joint history of previous diet and physical activity habits (ie, the hypothetical sustained intervention strategy) and confounding variables. For example, linear regression models are used to predict continuous covariates (eg, body weight), while logistic regressions are used to predict binary or categorical variables (eg, indicator variable for dietary supplement use). The per-protocol causal contrast of the hypothetical intervention presented in Table 2 is then emulated based on Monte Carlo simulated data generated using the g-formula algorithm [44]. The parametric g-formula correctly accounts for time-varying confounding in the presence of feedback between the intervention and the confounding variables, as confounding is addressed using standardization [41,42]. Furthermore, standardization allows for estimating an average causal effect (ie, marginal effect) consistent with the estimand of interest (equation 1) rather than a conditional effect. In summary, “threshold interventions” that depend on the reported dietary intakes or amount of physical activity [43,45] and the parametric g-formula [44,46] will be used to emulate the intervention of *consuming at least x servings of food* and *doing at least x minutes of light to vigorous physical activity.*

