### Limitations

The strengths of this study and protocol include the explicit emulation of a hypothetical trial, the thorough description of the emulation of the sustained dietary intervention, and the use of background knowledge and DAG to derive a sufficient set of confounders. Limitations must be addressed. First, the NuAge sample size is relatively limited (N=1753), although comprehensive nutrition and covariate data were collected. Second, the target food intakes based on diet simulations from Health Canada *exceeded* the 99th percentile of the usual intake distribution of Canadians aged ≥65 years from Canada in 2015 [3]. A revision of the dietary intervention targets may be needed if observed dietary intakes in NuAge deviate significantly from targets (Table 2), as was done in a previous nutrition target trial emulation [22]. Third, the presence of random measurement error associated with 24-hour dietary recalls may bias estimates. Finally, the target trial emulation cannot replace an actual RCT. Evidence from an RCT will be required to confirm the value of either CFG recommendations or the enhanced CFG recommendations.

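### Entering total intakes as covariates does not keep them constant across strategies in the primary Monte Carlo g-formula after baseline

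*Protocol article*

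**What the plan says.** The Implementation section describes the substitution twice. For the target trial, step 3 says that "participants would be instructed to decrease consumption of foods not recommended by the same amount as the increase in step 2". For the emulation, one total for food and one for beverages, both in RA/d, enter all models as covariates. Table 2, footnote a adds that "foods not recommended will be left out from the models". From this the section concludes: "Hence, total food and beverage intakes will be constant across hypothetical diet interventions".

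The primary contrast is per-protocol. Under Modeling of Hypothetical interventions, the g-formula and its R package "use parametric models to predict the joint history of previous diet and physical activity habits", together with the confounders. The contrast "is then emulated based on Monte Carlo simulated data generated using the g-formula algorithm". The interventions are thresholds on recommended foods and, in strategy 4, on physical activity. Table 2 gives no value for either total.

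The secondary intention-to-treat analog concerns "a hypothetical intervention in which adherence is measured at baseline only".

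On foods not recommended, Table 2, footnote d says that "consumption would be set at the smallest amount, permitting a concomitant increase in recommended foods", and that portions may differ between individuals. The Limitations section says: "A revision of the dietary intervention targets may be needed if observed dietary intakes in NuAge deviate significantly from targets (Table 2".

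**The concern.** The conclusion that totals are constant is drawn from one fact only, that they are covariates. Holding a covariate fixed is how a coefficient is interpreted. A g-formula simulation does not hold a variable fixed unless it is told to. If the totals are time-varying variables like the others, their values at time points 1 to 3 are predicted from a history in which recommended foods have been raised, and they respond to it.

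The per-protocol contrast would then combine the intended substitution with a change in the total amount eaten. The article itself, in its section on well-defined nutritional interventions, says that the handling of total intake affects the causal effect being estimated. The shift grows with the size of the dietary change, so it would tend to be larger in the extra-protein strategies that test hypothesis 2.

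A related gap concerns the remainder, that is, total minus recommended foods. It is the implied intake of foods not recommended. The substitution is one-for-one, and the article does not say what happens when a participant eats too little of these foods to give up.

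**Working it through.** The plan states no figure for this point, so there is none to reproduce.

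**1. Where the inference holds.** At time point 0 the total is observed. The threshold changes recommended foods and leaves the total alone. The intention-to-treat analog uses baseline only, so totals are constant there too.

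**2. Totals predicted before foods.** Let R be recommended foods, N foods not recommended and T = R + N. Let each of R and N depend only on its own previous value, with persistence ρ_R and ρ_N. Then

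E(T_k | T_{k−1}, R_{k−1}) = const + ρ_R·R_{k−1} + ρ_N·(T_{k−1} − R_{k−1}) = const + ρ_N·T_{k−1} + (ρ_R − ρ_N)·R_{k−1}.

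Raising R_{k−1} by D at fixed T_{k−1} shifts T_k by (ρ_R − ρ_N) × D, which is zero only if ρ_R = ρ_N.

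**3. Totals predicted after foods.** Let s be the same-visit slope of N on R, and D0 and D1 the increases in R at time points 0 and 1. The shift at time point 1 is (1 + s)·D1 − (ρ_N + s·ρ_R)·D0. With equal persistence and D1 = D0, this is zero only if s = −1.

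**4. Illustration. Every intake input is assumed, because the article reports no NuAge intakes.** There are four visits, pooled linear models with one lag, normal intakes and a separate threshold for each food.
- Mean RA/d for vegetables and fruits, whole grains, plant protein, animal protein and fats: men 4.5, 0.9, 0.6, 2.1, 0.8; women 4.5, 0.9, 0.5, 1.7, 0.7.
- SDs: 1.8, 0.7, 0.4, 0.8, 0.4.
- Foods not recommended: mean 3 (SD 1.5), 5 or 7 (SD 2), with correlation 0 or −0.4 with vegetables and fruits.

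Check of the formula for men with ρ_R = 0.7 and ρ_N = 0.4:
- Strategy 2: mean shortfall 3.37, so 0.3 × 3.37 = 1.01; simulated shift at time point 1 is 1.00 to 1.02.
- Strategy 3: mean shortfall 4.98, so 0.3 × 4.98 = 1.49; simulated 1.48 to 1.51.

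Difference in mean total food from the natural course at time point 3 (RA/d):

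| Set-up (ρ_R/ρ_N) | Men, strategy 2 | Men, 3 | Women, 2 | Women, 3 |
|---|---|---|---|---|
| Totals first, 0.6/0.6 | about 0 | about 0 | about 0 | about 0 |
| Totals first, 0.7/0.4 | +1.7 to +1.8 | +2.5 | +1.4 | +2.1 |
| Totals first, 0.4/0.7 | −2.2 to −2.3 | −3.3 to −3.4 | −1.7 to −1.8 | −2.7 to −2.8 |
| Totals after, all three pairs | +1.6 to +3.8 | +2.6 to +5.3 | +1.5 to +3.1 | +2.5 to +4.5 |

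A second simulation used one recommended-food variable with threshold 11.5, persistence 0.5 for both groups, and N falling by 0.2 per RA of R at the same visit. Differences at time points 0 to 3 were 0, −0.40, −0.63, −0.76 with totals first, and 0, +1.23, +1.84, +2.14 with totals after. So equal persistence is enough only when the groups do not otherwise influence each other. With each person's total set to its baseline value, the difference was 0.00 at every visit.

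**5. The remainder.** Food targets in Table 2, counting fats as food and milk as beverage:
- Strategy 2: men 6 + 1.5 + 1.0 + 2.0 + 1 = 11.5; women 5 + 1.5 + 0.8 + 1.5 + 1 = 9.8.
- Strategies 3 and 4: men 6 + 1.5 + 1.5 + 3.5 + 1 = 13.5; women 5 + 1.5 + 1.3 + 3.0 + 1 = 11.8.

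Anyone with total food below the sum has a negative remainder. Because intakes above a threshold stay as they are, the full condition is T < Σ max(food, threshold). With totals at natural-course values and the assumed intakes of step 4, the share of person-visits meeting this condition was 5–57% (men, strategy 2), 18–84% (men, 3), 2–41% (women, 2) and 10–72% (women, 3), as the mean of foods not recommended falls from 7 to 3 RA/d. In the second simulation, with totals fixed, about 25–29% were still negative. Holding totals constant therefore does not settle the remainder.

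**The case against.** The strongest reply is that the article states the property it wants and leaves the coding to the analysis. Total intakes are not in the list of time-varying covariates in the Assignment section, the examples of predicted covariates are body weight and supplement use, and the code will be public. The code may well set the totals, which would make the sentence true. That possibility stands. But the article gives a reason for constancy, covariate inclusion, and for the primary analysis that reason does not deliver it. No section says that totals are fixed or intervened on.

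A second reply is that, with totals predicted before foods, each visit's swap is still one-for-one at that visit's total, and later change is a consequence of the sustained strategy. As an estimand this is defensible, but it is not the one stated, which has constant totals across strategies.

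A third reply concerns the remainder. Footnote d and the foreseen target revision partly address targets that are out of reach. Step 3 also lets vegetables and fruits replace drinks, so the food-only shares overstate the shortage under that step, though not under separate constant totals. This stands.

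A reader might infer more: that totals in NuAge will drift by several RA/d, that many participants would be given impossible diets, or that a negative remainder would stay hidden. The documents do not support this. The intakes are assumed, the drifts take both signs and can be about zero, and the remainder is a plain subtraction of modelled variables. Nor does the article show that the targets of strategies 3 and 4 exceed the 90th percentile.

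**Conclusion.** The concern holds in a limited form. The sentence on constant totals is correct for coefficients, at time point 0 and for the intention-to-treat analog. For the primary per-protocol g-formula it does not follow from what is written. Totals at time points 1 to 3 shift unless they are set or special conditions hold; with totals modelled before foods, that condition is equal persistence of recommended and not-recommended foods in the own-lag model. This rests on the algebra and on reading the totals as predicted variables, since the article states no other treatment of them.

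Neither the size nor the sign of the drift, nor the share with a negative remainder, can be known from the article. The simulated figures are illustrative only. The planned comparison of observed with predicted covariates would not reveal drift that arises only under an intervention. Revising targets would lower the frequency of negative remainders but would not hold totals constant.

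**What to change.** 1. In the Monte Carlo step, set total food and total beverage to the same values under every strategy, for example each simulated person's natural-course values, and say so in place of the present inference. Otherwise withdraw the claim of constant totals and state that later changes in total intake are part of the estimated effect.
2. Compute the implied foods not recommended as total minus recommended foods, and report by strategy and sex how often it is below zero. Prepare this from exposure data alone, without outcomes, and use it for the target revision foreseen under Limitations.

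The cost is a little code and one table. A hard bound at zero is optional. It would need a rule for which target gives way when not all can be met at a constant total, and that is a design choice for the investigators.
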